**Subanalysis in the Randomized Trial**

A plasma monitoring study will be conducted on a subsample of the pragmatic clinical trial on LTBI randomly selected for the 100mg and 300mg drug presentation treatment arms of isoniazid from the Federal District sites. The subsample size will comprise 36 subjects (18 per arm of the pragmatic clinical trial).

The health units in which research participants will be invited to participate in the Federal District will be: Health Center of the Structural Administrative Region (1); Day Hospital 509 south (2); Pharmacy- School of the University Hospital of UnB (3). The first health unit is characterized by being a primary care unit located in a city of approximately 39,015 inhabitants (PDAD, 20151), the second being a specialized center both in the care network of the Health Department of the Federal District.

Brachial blood samples will be collected with a tube for serology in order to separate the total plasma in a centrifuge at 2500 rpm for 10 minutes and stored in a 1.5 mL Eppendorf tube at -80o C until the moment of measurement in the chromatography device. high performance liquid (HPLC). The samples will be sent for conservation at -80oC to the Biobank of the Nucleus of Tropical Medicine of the Faculty of Medicine of the University of Brasília (UnB) and later sent to the Toxicology Laboratory of the Department of Pharmacy of the Faculty of Health Sciences of the UnB.

Each research participant (n=36) will be invited, after reading, clarifying and signing the informed consent, to donate a blood sample at three different times of treatment (30 days of treatment; 3rd month of treatment; 6th month (at the end of ) treatment. Each plasma sample will be treated with solvent solution and filtered to prepare the specimen before performing the plasma isoniazid dosage. It will be launched in the HPLC in order to identify its chromatometric curve compared to the available isoniazid standard. In this way, it will be possible to identify the plasma level of isoniazid of participants with LTBI randomly allocated in the 100mg or 300mg arms of LTBI treatment with isoniazid in some possible subgroups: (i) patients with adequate adherence and use correctly foreseen by the Ministry da Saúde2; (ii) underdosage (those who, even with a 300mg prescription, can make a mistake and take a 100mg tablet thinking they are is receiving 300mg due to incorrect understanding or dispensing in a pharmacological presentation below the prescribed 300mg), (iii) overdose (participants who, due to a mistake in the participant's understanding, when using three 300mg tablets when it should have been 100mg); Possible drug interactions including those who are using other drugs, with any unexpected drug interactions; (iv) patients who did not correctly adhere to what was recommended and what was prescribed and informed by the prescriber even though the pharmacological presentation had been correctly dispensed.

Second stage

Study Scenario and Design

A cross-sectional study on knowledge, attitudes and practices (KAP) will be conducted. It is known that the triad of knowledge, attitudes and practices in combination regulate aspects of life in human societies. These three components can be defined as follows: Knowledge is the ability to acquire, retain and use information; a mixture of understanding, experience, insight and skill; Attitudes refer to inclinations to react in a certain way to certain situations; seeing and interpreting events according to certain predispositions; or organize opinions into coherent and interrelated structures; and Practices mean the application of rules and knowledge that lead to action. (Kaliyaperumal K., 2004). This methodology will be used in relation to prescribing and dispensing LTBI treatment, with a sample of primary care health professionals and reference units in Brasília, Curitiba, Santa Catarina, Ribeirão Preto and Espirito Santo.

**Participants and sample size**

All those involved will be invited to participate in prescribing, dispensing and monitoring LTBI treatment in primary care health units and reference units included in stage 1 in Brasília, Curitiba, Florianópolis, Ribeirão Preto and Vitória.

For the sample calculation, the STATA 15.0** program was used. A 70% hit ratio was considered, a power of 80% to detect differences and a significance level of 5%. Thus, it is estimated that 47 subjects are needed. As this is a cross-sectional study, the study design effect of 1.2 was applied. Therefore, 56 subjects will be needed.

**Data collect**

A single individual, self-administered, standardized and semi-structured questionnaire will be used for data collection. This questionnaire will contain questions with socio-demographic characteristics (sex, age, education, profession, family income, time since graduation, etc.) when, workload; if you received training on tuberculosis control, which type, when, workload; if you treat patients with tuberculosis or at least with respiratory symptoms; time in weeks of the last tuberculosis case treated; If you treat patients with LTBI, etc.). Included in Appendix 03

Data collection at all five study centers will be conducted prior to the qualitative focus group study to be conducted in Brasília.

**Assessment of knowledge, attitudes and practices**

We will establish as "knowledge about LTBI" for this study, the respondent who correctly answers at least five of the ten questions described below:

- Do patients with latent tuberculosis infection (LTBI) also have symptoms of pulmonary tuberculosis? Respondents are expected to respond negatively to this question.

- How would you make the laboratory diagnosis of LTBI? The interviewee is expected to answer: "mainly using the tuberculin skin test" and others such as IGRA mainly in patients vaccinated with BCG, in addition to the x-ray.

- How is the tuberculin skin test performed? The respondent is expected to respond: "(The antigen) is applied (0.1mL) intradermally (in the middle third) on the forearm)"

- How long does it take to get the tuberculin skin test result? Respondent is expected to respond: "(Preferably) within 48 to 72 hours of application"

- Would you answer that adults with a tuberculin skin test with a result above 5mm, but normal x-ray, should undergo treatment for LTBI? The respondent is expected to answer "Yes".

- Should children under 10 years of age, contact with a tuberculosis case, receive treatment for LTBI with a tuberculin skin test result > 10mm if vaccinated less than two years ago? The respondent is expected to answer: "Yes (they are even a priority)"

- Should the treatment for LTBI be the responsibility of the primary care service? Respondent is expected to answer "Yes"

- Is the treatment for LTBI conducted using isoniazid or rifampicin? Respondent is expected to answer "isoniazid"

- What is the maximum amount that a patient undergoing LTBI treatment should receive per day of the indicated drug? The respondent is expected to answer "300 mg/day".

- How long is the treatment for LTBI recommended? The respondent is expected to answer "six to nine months"

- In which situations is LTBI treatment recommended for people living with HIV/AIDS? The interviewee is expected to answer “Normal X-ray and PT >= 5mm, contact of a bacilliferous patient independent of PT and PT < 5mm and with a documentary record of having had PT >= and not undergoing chemoprophylaxis; radiological scar of TB without treatment record.

The 2011 Manual of Recommendations for Tuberculosis Control in Brazil (BRASIL, 20113) was used as the standard text for the preparation of the questions. Attitudes and practices will also be measured in an attached questionnaire.

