**Data analysis:**

The variables will be summarized using measures of frequency, and of central tendency and dispersion, being those that concern knowledge, attitudes and practices in the face of LTBI care. Categorical covariates will be tested using Pearson's chi-square test (or Fischer's Exact test) and continuous ones with Student's T test (or Wilcoxon) will be tested as factors associated with knowledge about LTBI. Variables tested in the bivariate analysis with p value < 0.20 will be taken to the multivariate analysis (logistic regression). In the end, it is expected to assume as factors associated with the lack of knowledge about LTBI those variables that, at the end of the multivariate analysis, present a value of p <0.05. Data will be collected through an electronic questionnaire with pre-coded and open questions, previously tested in a group of subjects similar to those included in the research to confirm the adequacy of the instrument, aiming at the quality of the information obtained.

Textual responses will be coded. The variables will be grouped as follows: adequate or sufficient and insufficient knowledge.

In the outcomes in relation to CAP, the variables will be grouped as follows: adequate or sufficient knowledge regarding the adequacy of the prescription in both doses and inadequate or insufficient knowledge, when knowing the adequacy of only one of the doses. The attitude will be considered adequate when it agrees with the indication of treatment for all the nominees and inappropriate when it does not agree or does not carry out the indication. Regarding the practice of indicating treatment, it will be divided into two groups: those that indicate treatment for LTBI (group 1) and those that do not (group 2).

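### Stage 2 looks for factors linked to LTBI knowledge only through a pass/fail cut at five correct answers, which discards information that the count of correct answers would keep

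*Protocol*

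**What the plan says.** All references are to the second stage of the protocol.

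- *Assessment of knowledge, attitudes and practices* lists knowledge questions with expected answers and sets the pass mark: "We will establish as 'knowledge about LTBI' for this study, the respondent who correctly answers at least five of the ten questions described below". Eleven questions follow; the last begins "In which situations is LTBI treatment recommended for people living with HIV/AIDS".
- *Data analysis* makes the result binary: "The variables will be grouped as follows: adequate or sufficient and insufficient knowledge". Categorical covariates are tested against knowledge about LTBI by chi-square or Fisher's exact test, and continuous ones by t test or Wilcoxon. Then: "Variables tested in the bivariate analysis with p value < 0.20 will be taken to the multivariate analysis (logistic regression". Factors with p < 0.05 in the final model are reported as associated with lack of knowledge. Central tendency and dispersion appear only as descriptive summaries.
- *Participants and sample size* gives the assumptions: "A 70% hit ratio was considered, a power of 80% to detect differences and a significance level of 5" per cent. The resulting figure of 47 is then inflated: "the study design effect of 1.2 was applied. Therefore, 56 subjects will be needed".

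The national manual is cited as the source of the questions, and the KAP guideline for defining knowledge, attitudes and practices. Neither is cited for the cut at five.

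**The concern.** The questionnaire yields an ordered count for each professional. After the cut, someone with 5 correct is treated like someone with 11, and someone with 4 like someone with 0. Differences within each group no longer help to show whether, say, earlier TB training goes with better knowledge.

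The survey is small. With 70% passing, about 0.30 × 56 = 16.8, or 17 respondents, would be classed as insufficient, and the logistic model draws on a long list of personal and professional characteristics. What is at stake is the chance of detecting real factors from the same respondents and the same answers. The protocol names both the outcome and the model, so this is a choice it makes and not a detail left to a separate analysis plan.

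**Working it through.** **1. The stated sample size.** Inputs from *Participants and sample size*: 70%, power 80%, alpha 5%. The comparison value is not stated; 50% is assumed because it reproduces the figure. For a two-sided one-sample test of a proportion:

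n = [(1.96·√(0.5·0.5) + 0.8416·√(0.7·0.3)) / 0.20]² = [(0.980 + 0.386) / 0.20]² = 46.6, so 47.

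47 × 1.2 = 56.4, stated as 56. The number therefore fits the estimation of one proportion. It was not derived for finding factors linked to knowledge.

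**2. Information kept by the cut.** Assume that the 70% is the share reaching five correct and that the score is roughly normal. The asymptotic efficiency of the yes/no outcome relative to the score is φ(z)² / [p(1−p)] with p = 0.30:

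φ(−0.524)² / (0.3 × 0.7) = 0.348² / 0.21 = 0.576.

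56 × 0.576 = 32, so 56 respondents give about the information that 32 would give if the score were analysed.

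**3. Power with discrete counts.** The protocol gives none of the inputs needed, so these are assumptions: 28 v 28 independent respondents; 11 items; each person's chance of a correct answer = expit(μ + sd·z + β·x), with z standard normal and x the factor; μ set so that 70% overall score at least 5; two-sided 5%; 6000 replicates. The score is compared by t test and the cut by Pearson chi-square.

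| Between-person sd | β (log-odds) | Score power | Cut power | Loss (points) |
| --- | --- | --- | --- | --- |
| 0.5 | 0.5 | 64% | 44% | 20 |
| 0.5 | 0.7 | 89% | 69% | 20 |
| 0.8 | 0.5 | 43% | 29% | 14 |
| 0.8 | 0.7 | 70% | 50% | 20 |
| 0.8 | 0.9 | 89% | 70% | 19 |
| 1.1 | 0.5 | 30% | 21% | 9 |
| 1.1 | 0.7 | 51% | 35% | 16 |
| 1.1 | 0.9 | 71% | 51% | 20 |
| 1.1 | 1.1 | 88% | 69% | 19 |

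At sd 0.8 the three effects correspond to differences of about 1.2, 1.7 and 2.1 items. Repeat runs move each power by about a point, so the loss is best given as about 9 to 21 points. With no effect, both tests reject close to 5% of the time.

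**4. How far the range moves.**

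- Small effects (β 0.3, sd 0.8 or 1.1): loss about 3 to 5 points. A very large effect (β 1.1, sd 0.5): about 3 points.
- Fisher's exact test, which the protocol also allows: about 16 to 33 points over the effects in the table.
- A continuous normal score instead of 11 discrete items, 70% passing: 26% v 16% at 0.35 SD, 46% v 28% at 0.5 SD, 80% v 54% at 0.75 SD, so about 10 to 26 points.
- The same model with other pass rates: at 50% passing, losses of 8 points at 0.35 SD and 21 at 0.7 SD; at 80% passing, 22 points at 0.5 SD and 34 at 0.75 SD.
- Design effect: 56 / 1.2 = 46.7. With 47 independent respondents, the 1.2-item case gives about 37% v 25%, so both powers fall.
- If the 70% were instead the chance of a correct answer per item, with independent items, P(at least 5 of 10) = 0.953, and 56 × 0.047 = 2.6, or about 3 respondents, would be insufficient. The pass/fail model would then have almost nothing to work with.

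**The case against.** The strongest reply is that the pass mark is the question. The protocol looks for factors associated with lack of knowledge, and a factor that moves people from 8 to 10 correct says little about who lacks it. A difference in mean correct answers is a different estimand, so the comparison of power is partly between two questions. This stands, and it is a reason to keep the pass/fail model as a secondary analysis. It does not justify making that model the only one, because no reason is given why four versus five correct should decide. That the count weights easy and hard items equally is no defence either, since the pass mark is built from the same count.

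Four limits also stand. The survey invites everyone involved, so 56 is a minimum and not a cap. The simulation tests one factor alone and not the planned p < 0.20 screen followed by a multivariable model. Finding factors for knowledge is an analysis step and is not among the protocol's listed objectives. And *Data analysis* also defines adequate knowledge by familiarity with both presentations, for prescribers and for dispensers. Those categories have no count behind them, so this point does not reach them. The reading here rests on the regression being described as concerning knowledge about LTBI, which is the term defined by the cut.

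**Conclusion.** The point holds in a conditional form. The protocol cuts an available count at five and bases its search for factors on the yes/no result alone. At 70% passing, that keeps about 58% of the information in an approximately normal score. Under the assumptions in the table, it costs about 9 to 21 points of power where the score has roughly 30% to 90% power, less at the extremes and more with Fisher's exact test.

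A reader might infer that the protocol itself implies a fixed loss of that size. It does not: effect size, score spread, factor prevalence and the meaning of the 70% are all absent, and other plausible assumptions give other ranges. Nor do the documents support the inference that every knowledge analysis in stage 2 is affected, or that the randomized comparison is. This is a worthwhile, inexpensive improvement to a secondary stage.

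**What to change.** In the second-stage *Data analysis* section, for the knowledge questionnaire only:

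- make the number of correct answers the outcome of the factor analysis, using linear regression with robust standard errors or proportional-odds regression, with effects and 95% CIs;
- report the proportion with at least five correct, with its 95% CI, as the descriptive summary;
- if wanted, keep the pass/fail logistic model as a secondary analysis, labelled as such.

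State how many items enter the count, since the definition says ten and eleven are listed. Leave the both-presentations categories as they are.

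The cost is a change of wording, with no extra respondents or data. The downside is that factor effects are expressed as a difference in number correct, or an ordinal odds ratio, and not as an odds ratio for lacking knowledge.

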Similarly, professionals who participate in the dispensing process at baseline will be evaluated. The variables will be grouped as follows: adequate or sufficient knowledge, when the professional is able to identify the use of Isoniazid 100mg and use of Isonizaide 300mg and inadequate or insufficient, when knowing the indication for the use of only one of the doses. The attitude will be considered appropriate when in possession of the prescription, the professional checks the presentation of Isoniazid and inappropriate when not checking before dispensing the drug. Regarding the practice, it will be divided into two groups: those who keep the two presentations in different places (group 1) and those who keep the two presentations in the same place (group 2).

[figure not shown]

[figure not shown]

[figure not shown]

[figure not shown]

[figure not shown]

[figure not shown]

[figure not shown]

[figure not shown]

[figure not shown]

Figure 3- timeline for selecting the study sample

Third Stage

It will be a qualitative research that, according to Denzin and Lincoln (2006), involves an interpretive approach to the world, which means that its researchers study things in their natural settings, trying to understand phenomena in terms of the meanings that people give to them. The theoretical axis adopted will be that of social representations, understood as modalities of practical knowledge, oriented towards communication and understanding of the social, material and ideational context in which we live.

The contents expressed by the individual are essentially heterogeneous; they translate the thinking, the common sense of a given social group, understanding the individual in a social perspective, because reality is socially constructed (SPINK, 2004). For Marx (1994) the human essence is not something abstract and immanent to each individual. It is, a reality, built in the set of social relationships that can be reported, can be observed; the speeches and experiences of social actors provide relevant data for the researcher, through meetings and conversations, to expand access to the production of meaning and the representations of individuals constructed (SPINK, 2004).

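### Stage 2 models only a general LTBI knowledge score that contains nothing on the 100mg and 300mg presentations, although its objectives concern prescribing and dispensing Isoniazid 300mg

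*Protocol*

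**What the plan says.** All places are in the Protocol.

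- **Objective.** Two objectives are to be met through the knowledge, attitudes and practices survey: compliance in prescribing Isoniazid 300mg and compliance in dispensing it.
- **Assessment of knowledge, attitudes and practices.** Knowledge about LTBI is credited to "the respondent who correctly answers at least five of the ten questions described below". The list covers symptoms, laboratory diagnosis, skin-test technique and reading time, indications in adults and children, level of care, choice of drug, daily maximum, duration, and indications in people with HIV.
- **Data analysis, modelling.** Covariates are tested for association with knowledge about LTBI. Those with p < 0.20 go into a logistic regression, and those with p < 0.05 at the end are taken as factors associated with lack of knowledge about LTBI.
- **Data analysis, prescribers.** For the survey outcomes, knowledge is grouped as "adequate or sufficient knowledge regarding the adequacy of the prescription in both doses and inadequate or insufficient knowledge, when knowing the adequacy of only one".
- **Data analysis, dispensers.** Knowledge is adequate "when the professional is able to identify the use of Isoniazid 100mg and use of Isonizaide 300mg", and insufficient when the use of only one is known.
- **Participants and sample size.** "A 70% hit ratio was considered, a power of 80% to detect differences and a significance level of 5" percent; the result is 47 subjects, raised to 56 by a design effect of 1.2.

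**The concern.** The survey has two measures that both carry the name knowledge, and both are split into adequate and insufficient. One is a pass mark on general LTBI questions. The other asks whether the professional knows both presentations. No sentence says how they relate or which serves the 300mg objectives.

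The only regression planned within this stage takes the general score as its outcome. A professional unaware of the 300mg tablet can pass that score and count as knowledgeable in the model. The Introduction explains why this matters: two presentations will be in use side by side, and overdose can cause severe harm. Factors associated with not knowing how a skin test is read do not show where confusion between presentations is likely.

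**Working it through.** **1. What the general score contains.** Counting the listed questions gives eleven, not ten. None asks about tablet presentations. One has 300 mg/day as its expected answer, but that is the daily maximum, not the tablet. The questions are based on a 2011 manual, while the Introduction says the 300mg presentation becomes available from 2018.

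The item count affects the pass mark. If each item were answered correctly with probability 0.5, independently (an assumption), the chance of at least five correct is:
- ten items: 1 − 386/1024 = 62.3%
- eleven items: 1 − 562/2048 = 72.6%

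**2. Whether the two measures can differ.** Take a prescriber who answers five general questions correctly and knows only the 100mg presentation. The score says knowledgeable; the classification says insufficient. They always agree only if passing the score and knowing both presentations coincide for every respondent.

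**3. Which measure is modelled.** The bivariate tests and the regression both use the term defined by the general score. The both-presentations classification enters no stated model.

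**4. Completeness of the classification.** Both presentations known is adequate; only one known is insufficient. Neither known has no category, in the prescriber rule or the dispenser rule.

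**5. The stated sample size.** The protocol gives no null proportion and no sidedness. Assume a one-sample test of 70% against 50%, two-sided 5%, 80% power:

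n = [(1.96 × √(0.5 × 0.5) + 0.8416 × √(0.7 × 0.3)) / (0.7 − 0.5)]² = 46.6, so 47.

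Then 46.63 × 1.2 = 55.95, so 56. The stated figures are reproduced. A null of 45% gives 30 and one of 55% gives 83, so 50% is a plausible inference, but it is not in the text. Nothing ties the 70% to either knowledge measure.

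**6. Illustration of disagreement (assumed rates).** Let 70% pass the general score and let q know both presentations, with q from 0.3 to 0.6. The protocol gives no value for q, and assigning the 70% to the general score is also an assumption.
- If everyone who knows both also passes the score, disagreement is 0.7 − q, which is 40% to 10%, or 22 to 6 of 56.
- If the two are independent, it is 0.7(1 − q) + 0.3q, which is 58% to 46%, or 32 to 26 of 56.

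**7. Room for a model.** With 56 respondents the smaller outcome group is at most 56 × 0.5 = 28. It is about 56 × 0.3 = 17 if the split is 70/30.

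**The case against.** The strongest reply is that these are two constructs with two labels. The general score is introduced as knowledge about LTBI; the other rule opens a separate paragraph on the survey outcomes and concerns the prescription in both doses. The second stage's scope is prescribing and dispensing LTBI treatment, so general knowledge belongs in it. The objectives ask to analyse compliance, not to run a regression on 300mg knowledge, and the both-presentations groupings can be reported descriptively.

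Much of this stands. A reader might infer that the protocol contradicts itself, or that an analyst could choose the regression outcome after seeing the data. The text does not support either: the labels differ, and the regression outcome is named. Disagreement between two constructs is expected and is not a count of errors.

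A reader might also infer a loss of power. With a true rate of 60% and 47 subjects, power against 50% would be 27%. That follows from an assumed rate and an assumed null, and any outcome with a lower rate would show it. It does not measure harm from having two measures.

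The appendices, including the questionnaire, are not shown, and they may set out how items map to each measure. They would not change which measure the protocol names for its regression. What the reply does not remove is that the modelled score, as listed, cannot reveal lack of knowledge of the new presentation, and that knowing neither presentation has no category.

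**Conclusion.** The point holds as a mismatch between analysis and objective. The associated-factors analysis uses a general score with no item on the presentations, while the two survey objectives concern Isoniazid 300mg. Three smaller faults go with it: ten questions are announced and eleven listed, professionals who know neither presentation are unclassified, and the 70% in the sample size is not attached to a named measure.

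These conclusions rest on the text alone, reading both doses in the prescriber rule as the 100mg and 300mg presentations. The disagreement figures are illustrative and depend on rates that the protocol does not give. The sample size arithmetic is not at fault. The weight is limited, because this is a survey alongside the trial and the randomised comparison and its primary outcome are untouched.

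**What to change.** 1. Label the pass-mark score general LTBI knowledge, correct its item count, and restate the pass mark against that count.
2. Name the both-presentations classification, in its prescriber and dispenser forms, as the knowledge outcome for the two 300mg objectives. Score knowing neither presentation as insufficient.
3. Fit the associated-factors model to that outcome with professional role (prescriber or dispenser) as a covariate. Keep any model of general knowledge as secondary.
4. In Participants and sample size, state which measure the 70% and the 80% power refer to, and the null proportion.

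**Cost.** The change is one of wording and analysis. The classification is already a planned outcome, so no new data should be needed, provided the questionnaire (not shown) captures it. With about 56 respondents the model supports few covariates. A role term allows for a difference in level between prescribers and dispensers, but not for factors that act differently in the two groups. The stated 80% power may need restating for the named outcome.
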